##### Quantitative research questions

What effect does the intervention have on the participants’ ability to work, as measured by the Work Ability Index (WAI)?What effect does the intervention have on quality of life as measured by the WHO Quality of Life-BREF (WHOQOL-BREF)?What effect does the intervention have on perceived stress levels as measured by the Depression Anxiety Stress Scale-21 (DASS-21)?Is there a correlation between the level of digital health literacy, measured with the G-eHEALS and a holistic DHL instrument, and postintervention levels of workability, quality of life and perceived stress?

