#### Stage 2: piloting (September 2023–December 2023)

In stage 2 (S2), we aim to answer the central research question: How should the psychosocial prevention intervention ‘RV Fit Mental Health’ be implemented?

We will pilot the intervention and assess its feasibility. Thus, three research objectives emerged for stage 2. First, the needs and experiences of the participants will be analysed to identify standards for addressing potential participants and to optimise the intervention. Second, the constructed instrument for evaluating the intervention will undergo a pretest and a feasibility assessment. As the instrument will include an assessment of DHL, we aim to identify additional skills, competencies and prerequisites that need to be analysed to predict effectiveness. This results in five qualitative and one quantitative subresearch questions for stage 2.

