### Quantitative data collection

Quantitative data will be collected from the study participants in S2 and S3 at four different points (t0–t3) through (online) surveys, depicted graphically in figure 3.

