**Figure 3 F3:**
[figure not shown]
Overview of quantitative data collection.

t0 (first survey) transpires when insured persons are confirmed that participation in the prevention intervention is possible.t1 (second survey) takes place at the beginning of the prevention intervention within the first 2 days of the initial inpatient phase.t2 (third survey) is conducted 2 weeks after t1, at the end of the initial inpatient phase.t3 (fourth survey) occurs 12 weeks after the inpatient phase at the end of the 12-week training phase.

The primary outcomes of interest are workability, assessed using the German Work Ability Index^70^; quality of life, using the German WHO Quality of Life-BREF^71 72^; stress levels, evaluated using the Depression Anxiety Stress Scale-21 (DASS-21)^73–75^ and eHealth literacy, which will be assessed using the G-eHEALS^76–78^ and a self-developed instrument for holistic DHL. The secondary outcomes are anxiety and depressive symptoms (DASS-21) and self-efficacy using the SWOP K9.^79–82^ Further information on the validity and reliability of the assessment instruments is provided in ‘online supplemental material 1’. In addition, we are interested in health behaviour as a secondary outcome, which we operationalise as alcohol consumption, smoking, physical activity and dietary behaviour. The training phase behavioural data follow the FITT criteria^83 84^: frequency, intensity, time and type. We will use FITT data to examine participants’ adherence to the eHealth application.^85^ Additionally, sociodemographic data will be collected during survey t1, and behavioural data from the training phase will be gathered during survey t3.

10.1136/bmjopen-2023-081390.supp1Supplementary data

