#### Quantitative analysis

Quantitative data analysis will be conducted using the IBM SPSS software (Version 29.0.1.0). During S2, the dataset will undergo a preliminary examination for meaningfulness. This involves checking for the data’s completeness, outliers and plausibility. A descriptive characterisation of the quantitative S2 sample will be performed based on sociodemographic data to gain initial insights into the sample.

For S3, we plan a pre–post design effectiveness evaluation. The baseline data will be compared with the data from t1 to t3. For this, we will conduct multifactorial variance analyses to investigate whether there are differences in the groups of individual intervention time points regarding the primary and secondary outcomes, thus demonstrating the potential effect of the prevention intervention. Additionally, we will perform regression analyses to interpret the relationship between the collected variables, allowing for statements about the influence of individual variables on different outcomes. Similarly, we present a differentiated sample characterisation for S3. In addition, we add a waitlist-controlled component. After collecting data from t0 to t4, we divide participants of S3 into an intervention and waitlist group. We conduct t-tests within each group to analyse the effects between t0 and t1 for the waitlist group and between t1 and t3 for the intervention group. Calculating Cohen’s d helps us quantify effect sizes from these tests. We then use a Z-test to compare Cohen’s d values of both groups to determine if there are significant differences in effect sizes.

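### Question 4 relates digital health literacy to post-intervention scores with no stated role for the pre-intervention score, so an existing difference can pass for a link with outcome

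*Protocol article*

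**What the plan says.** In the Protocol article, the stage 3 section on quantitative research questions puts three questions about the effect of the intervention. The fourth is of a different kind and asks only for a correlation. Its two sides are literacy scores "measured with the G-eHEALS and a holistic DHL instrument, and postintervention levels of workability, quality of life and perceived stress". The outcome side is the post-intervention level. Neither change nor the starting value is mentioned.

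The only planned method that could serve this question is in the quantitative analysis section: "we will perform regression analyses to interpret the relationship between the collected variables", with the stated purpose of "allowing for statements about the influence of individual variables on different outcomes". Covariates are not listed, so a baseline term is neither stated nor excluded.

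Two other places bear on the purpose and on feasibility. The stage 2 section, in explaining why literacy is part of the instrument, says "we aim to identify additional skills, competencies and prerequisites that need to be analysed to predict effectiveness". The data collection section says "Quantitative data will be collected from the study participants in S2 and S3 at four different points (t0–t3) through (online) surveys". Of these surveys, t0 falls at confirmation of a place and t1 within the first two days of the inpatient phase, so outcome values from before or at the very start of the intervention are available.

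**The concern.** People with higher digital health literacy may already have better work ability, better quality of life and less stress when they enter the programme. Scores of this kind are usually correlated over time, so such a difference would still be visible at t3. A correlation of literacy with the t3 score then mixes two things: where people started, and how they fared from there. Only the second bears on whether literacy predicts how well the programme works.

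The article's own language invites the second reading, since it speaks of influence on outcomes and of predicting effectiveness. If question 4 is answered as worded, a significant crude correlation could be reported in those terms when it reflects only the starting position. The large planned sample adds to the risk, because even a small correlation is likely to reach significance.

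**Working it through.** The Protocol article states no alpha, correlation or power for this question, so there is no figure of its own to reproduce. The following is an illustration under stated assumptions.

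**Inputs**
- Sample size: 960 planned for stage 3 (section on the quantitative sample). Drop-out is expected but no rate is given. Assumed losses of 0%, 30% and 50% give 960, 960 × 0.7 = 672 and 960 × 0.5 = 480.
- Correlation of literacy with the pre-score, r_DB: not given; assumed 0, 0.1, 0.2, 0.3.
- Correlation of pre-score with post-score, r_BP: not given; assumed 0.5 and 0.7.
- Two-sided alpha 0.05: assumed.
- Literacy has no link with the post-score once the pre-score is known.

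**Step 1: crude correlation.** Under the last assumption, corr(literacy, post) = r_DB × r_BP. The range is 0.1 × 0.5 = 0.05 to 0.3 × 0.7 = 0.21.

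**Step 2: chance of significance.** By Fisher's z, m = atanh(r) × √(n − 3), and the chance is Φ(m − 1.96) + Φ(−m − 1.96). For r = 0.05 and n = 960, m = 0.0500 × √957 = 0.0500 × 30.94 = 1.55, and Φ(1.55 − 1.96) = Φ(−0.41) = 0.34.

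| r_DB | r_BP | crude r | n = 960 | n = 672 | n = 480 |
|---|---|---|---|---|---|
| 0 | either | 0 | 0.05 | 0.05 | 0.05 |
| 0.1 | 0.5 | 0.05 | 0.34 | 0.25 | 0.19 |
| 0.1 | 0.7 | 0.07 | 0.58 | 0.44 | 0.33 |
| 0.2 | 0.5 | 0.10 | 0.87 | 0.74 | 0.59 |
| 0.2 | 0.7 | 0.14 | 0.99 | 0.95 | 0.87 |
| 0.3 | 0.5 | 0.15 | 1.00 | 0.97 | 0.91 |
| 0.3 | 0.7 | 0.21 | 1.00 | 1.00 | 1.00 |

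Each figure applies to one literacy instrument paired with one outcome.

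**Step 3: simulation of three analyses.** 1500 runs at n = 960, with no link of literacy to outcome beyond baseline. Rejection rates:

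| r_DB, r_BP | post on literacy | post on literacy and pre | change on literacy |
|---|---|---|---|
| 0.1, 0.5 | 0.35 | 0.06 | 0.34 |
| 0.2, 0.5 | 0.86 | 0.05 | 0.88 |
| 0.2, 0.7 | 1.00 | 0.05 | 0.66 |
| 0.3, 0.7 | 1.00 | 0.04 | 0.96 |

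The crude column agrees with step 2. The adjusted column stays near 0.05.

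**Step 4: why the change score fails.** With equal pre and post variances, corr(literacy, post − pre) = −r_DB × √((1 − r_BP)/2). For 0.2 and 0.7 this is −0.2 × √0.15 = −0.077. The sign is reversed: higher literacy would seem to go with a smaller gain, again only because of the starting position.

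**The case against.** The strongest reply is that a research question is not a model. Question 4 names no test and no covariates. The regressions in the analysis section could contain the pre-score, and a condensed article may leave the covariate list to the full protocol or analysis plan. A reader might infer that the plan excludes baseline adjustment; the document does not support that, and silence on covariates alone would be no finding. What remains is that the published question fixes its target as "postintervention levels of workability, quality of life and perceived stress". A baseline-adjusted regression answers a different question from that one.

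Second, question 4 asks only for a correlation, and a crude correlation answers it literally. This stands as far as the question goes. The effect reading comes from the analysis section and, less directly, from stage 2, where the sentence on predicting effectiveness concerns additional skills and prerequisites.

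Third, the distortion is conditional. A reader might infer that existing differences will look like an effect of literacy. That needs literacy to be correlated with the pre-scores, and the documents give no figure; at zero correlation nothing goes wrong.

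Fourth, one might suspect that literacy is taken after the app phase and altered by app use. The text does not say which measurement question 4 uses, and the figure with the survey overview is not shown, so this is a possibility and not an error found.

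Finally, the data collection section lists among the primary outcomes "eHealth literacy, which will be assessed using the G-eHEALS" and a self-developed instrument, while question 4 treats literacy as a predictor. A reader might conclude that literacy should come off the primary list. That does not follow. A variable can have both roles, and the variance analyses are planned for all primary and secondary outcomes, so change in literacy is analysed even without its own research question.

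**Conclusion.** The point holds in conditional form. As worded, question 4 targets raw post-intervention levels, no section brings in the pre-score, and the analysis section means to speak of influence. If literacy is related to the starting scores, the crude analysis can declare a link where there is none beyond baseline. At n = 960 the chance is about 34% to 100% over the assumed ranges (19% to 100% at 480), against 5% when literacy and baseline are uncorrelated. With the pre-score in the model it is 4% to 6% in simulation.

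These figures rest on assumed correlations, an assumed 5% level, and no link of literacy to outcome given the measured pre-score. They show how large the problem could be, not that it will occur.

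One should not read more into the adjusted result either. It shows whether literacy predicts the t3 score beyond the starting score. By itself it does not show that literacy changes the effect of the intervention, since that would need a comparison with people not receiving it.

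**What to change.** State that question 4 is answered, for each outcome, by regressing the t3 score on literacy measured before the intervention, with the t1 score of the same outcome as covariate. Base any statement about influence on that coefficient. If the unadjusted correlation is also reported, label it descriptive. Do not use an unadjusted change score in place of the covariate.

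The cost is a sentence or two of wording. The planned t1 to t3 comparison already requires the t1 outcome scores. Because literacy is itself a primary outcome in the pre-post analysis, a pre-intervention literacy value should exist as well; the sponsor should name which survey supplies it. The list of primary outcomes need not change for this point.

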### Intervention participants and study sampling

#### Participants in the prevention intervention

There are two pathways through which individuals are recruited for the prevention intervention. Pathway 1 is carried out by the German Pension Insurance Central Germany, a regional institution responsible for two million employed people and over one million pensioners. Pathway 2 is carried out by the health insurance companies AOK SAN and AOK PLUS, regional institutions of the Health Insurance AOK in the east of Germany, insuring a combined 4.3 million citizens. The three insurance companies will contact eligible insureds and proactively suggest the RV Fit Mental Health prevention intervention.

#### Sample and recruitment for all study stages

##### Qualitative sample: participants of the intervention (S2, S3)

Focus groups (FG) with intervention participants will be conducted during the piloting (S2) and evaluation (S3) stages. We will sample through a random sampling method, where data collection time points will be predetermined. We plan four FG in the S2 with 6–10 participants each. Ten FG, also with 6–10 participants each, are planned in S3. Overall, we plan up to 14 FG with intervention participants. Contact with the individual group participants for the qualitative data collection is initiated via the respective clinic staff. If there is interest in participation, the clinics forward the time and number of participants. Inclusion criteria are the participation in the prevention intervention and sufficient German language skills.

##### Qualitative sample: experts (S1, S2, S3)

Expert interviews with representatives of the German Pension Insurance Central Germany, the AOK SAN, and AOK Plus, and with the executing healthcare professionals from the intervention clinics, will be conducted during the development (S1) and evaluation (S3) stages. There will also be FG in the pilot (S2) stage with these experts. Experts involved in planning and conducting the intervention are included in all stages. Inclusion criteria are the involvement in the development and/or implementation of the intervention, either organisationally or therapeutically. Up to 10 participants will participate in each point of the data collection. The TUM project team will proactively recruit the participants of the expert interviews and the FG.

Furthermore, additional expert interviews will be conducted in S2. Included are healthcare professionals (this may include physicians, psychologists and psychotherapists) who have prescribed or recommended app-based (digital) health applications for disease management, health promotion or prevention as part of a treatment pathway, individuals who are involved in health research regarding the topic of digital health and DHL as well as individuals from health policy in the field of digital health. Excluded are individuals who have prescribed, recommended or are experienced in other digital health technologies, such as wearables (smartwatches, trackers, etc), and people who do not work in healthcare. We will interview 10–12 experts. The experts will be recruited via professional associations and proactively through the study team.

##### Quantitative sample: participants of the intervention (S2, S3)

We aim to survey all participants from the intervention’s piloting (S2) and evaluation (S3) stages. We will use a non-probability sample for recruitment. Participants in the prevention intervention will receive a flyer on recruitment for our study via the German Pension Insurance and the intervention clinics. On the flyer are instructions and online access for our quantitative data collection. In S2, we expect a total of 60 participants. In S3, we intend to include 960 participants for the pre–post design effectiveness assessment. Inclusion criteria are the participation in the prevention intervention and sufficient German language skills. We expect drop-outs, especially during the digital training phase.

### Data collection

#### Qualitative data collection

The overall qualitative data collection is depicted graphically in figure 2.

**Figure 2 F2:**
[figure not shown]
Overview of qualitative data collection.

The FG with participants occur both during the initial inpatient phase on-site at the clinics and online during the digital training phase. The FG in the inpatient phase occurs towards the end of the inpatient stay. The online FG takes place when at least 4 weeks of the digital training phase have been completed.

The interviews with the experts will be conducted online. Depending on the research questions in each stage, a semistructured interview guide will be developed and pretested for each expert group. The interview guides will be developed following the principles of Helfferich.^65^ Furthermore, we are following the methodical principles of expert interviews and recognise the context of the new intervention as well as the evaluative character of the expert interviews.^66–68^

The FG with the experts will take place during a project workshop on-site. The FG is based on a purposive moderation guide starting with a stimulus recognising the specified topics, the organisational contexts and the environment of the intervention.^69^

### Quantitative data collection

Quantitative data will be collected from the study participants in S2 and S3 at four different points (t0–t3) through (online) surveys, depicted graphically in figure 3.

**Figure 3 F3:**
[figure not shown]
Overview of quantitative data collection.

t0 (first survey) transpires when insured persons are confirmed that participation in the prevention intervention is possible.t1 (second survey) takes place at the beginning of the prevention intervention within the first 2 days of the initial inpatient phase.t2 (third survey) is conducted 2 weeks after t1, at the end of the initial inpatient phase.t3 (fourth survey) occurs 12 weeks after the inpatient phase at the end of the 12-week training phase.

The primary outcomes of interest are workability, assessed using the German Work Ability Index^70^; quality of life, using the German WHO Quality of Life-BREF^71 72^; stress levels, evaluated using the Depression Anxiety Stress Scale-21 (DASS-21)^73–75^ and eHealth literacy, which will be assessed using the G-eHEALS^76–78^ and a self-developed instrument for holistic DHL. The secondary outcomes are anxiety and depressive symptoms (DASS-21) and self-efficacy using the SWOP K9.^79–82^ Further information on the validity and reliability of the assessment instruments is provided in ‘online supplemental material 1’. In addition, we are interested in health behaviour as a secondary outcome, which we operationalise as alcohol consumption, smoking, physical activity and dietary behaviour. The training phase behavioural data follow the FITT criteria^83 84^: frequency, intensity, time and type. We will use FITT data to examine participants’ adherence to the eHealth application.^85^ Additionally, sociodemographic data will be collected during survey t1, and behavioural data from the training phase will be gathered during survey t3.

10.1136/bmjopen-2023-081390.supp1Supplementary data

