### Problem summary

In summary, the following problems were identified: first, stress experienced by individuals related to or exacerbated by the work environment can become chronic, negatively affecting their mental and physical well-being. Consequently, this places an increasing burden on the healthcare systems. Second, prevention interventions can protect against the chronification of stress; however, prevention interventions are rarely taken up in Germany. Third, digitally enabled prevention interventions can increase utilisation. However, it cannot be assumed that different people can use digital health applications equally effectively. Fourth, there are measurement tools for assessing DHL, but existing measurement tools do not account for potential determinants that may impact the effective use of digital health applications. Fifth, regarding developing and implementing a new digital intervention, there is a need to analyse the acceptance and contextual factors.

The study aims to investigate the development, piloting and evaluation of a psychosocial app-based prevention intervention using a comprehensive mixed-methods approach. The intervention explicitly focused on mental health problems related to or exacerbated by the work environment, such as affective disorders, phobic and other anxiety disorders, adjustment disorders, somatoform disorders and burn-out. Its main aim is to improve the participation of those affected in their working life. The study protocol was developed using the ‘Standard Protocol Items: Recommendations for international trials’ (SPIRIT) checklist.^55^

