#### Stage 3: evaluation (January 2023–April 2026)

Stage 3 (S3) aims to analyse the implementation and execution of the intervention. The key research questions in the evaluation stage are: (1) Is the implementation of the psychosocial prevention intervention achieved? and (2) Is the psychosocial prevention intervention successful?

We will examine organisational conditions, accessibility of the target group and collaboration among the project partners to implement the prevention intervention. We will investigate this from the perspectives of professionals and intervention participants. Additionally, we will assess the effectiveness of the intervention. This results in six qualitative and four quantitative subresearch questions for stage 3.

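### Digital health literacy is a primary outcome in one section and only a correlate in another, and the primary outcomes tested for effect have no ranking and no leading time contrast

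*Protocol article*

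**What the plan says.** Four places in the protocol article bear on this.

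- **Quantitative data collection (text under Figure 3).** The list begins "The primary outcomes of interest are workability, assessed using the German Work Ability Index", continues with "quality of life, using the German WHO Quality of Life-BREF" and the stress scale of the DASS-21, and ends with eHealth literacy, measured by the G-eHEALS "and a self-developed instrument for holistic DHL". That is four constructs on five instruments, in no stated order of importance.
- **Quantitative analysis.** Baseline is compared with t1 to t3 by multifactorial variance analyses for the primary and secondary outcomes, and differences are taken to show the potential effect of the intervention. No time point leads. A separate waitlist component uses t0 to t1 for the waitlist group and t1 to t3 for the intervention group.
- **Stage 3, quantitative research questions.** Questions 1 to 3 ask for the effect on the WAI, the WHOQOL-BREF and DASS-21 stress, one each. Question 4 asks: "Is there a correlation between the level of digital health literacy, measured with the G-eHEALS and a holistic DHL instrument, and postintervention levels of workability", and likewise quality of life and stress.
- **Stage 3, evaluation.** The second key question is given as "2) Is the psychosocial prevention intervention successful". No criterion for a positive answer follows.

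**The concern.** A primary outcome is the quantity on which a claim of effect rests. Digital health literacy has that status in the outcome list, and the analysis section would test it for change like the other primaries. The research questions never ask whether the intervention changes it. They treat it as something that may explain the level of the other three. A reader cannot tell whether a rise in the G-eHEALS score would count towards effectiveness.

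The second part concerns the remaining outcomes. With several primaries of equal standing and several time points, the article does not fix which result carries the effectiveness conclusion. That choice would then remain open once stage 3 results are seen.

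**Working it through.** **Step 1: the role of each outcome, section by section.**

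| Outcome | Outcome list | Stage 3 questions | Quantitative analysis |
|---|---|---|---|
| WAI | primary | effect (question 1) | tested over time |
| WHOQOL-BREF | primary | effect (question 2) | tested over time |
| DASS-21 stress | primary | effect (question 3) | tested over time |
| G-eHEALS | primary | correlate only (question 4) | tested over time, as a primary |
| Holistic DHL instrument | primary | correlate only (question 4) | tested over time, as a primary |

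The first three rows agree across the columns. The last two do not.

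**Step 2: the time contrasts.** The survey schedule places t0 at confirmation of eligibility, t1 in the opening two days of the inpatient stay, t2 at its end and t3 at the end of the training phase. The article does not define baseline. If it is t0, the comparisons are t0 with t1, t2 and t3. The first lies almost wholly before the intervention, and the waitlist component uses that same interval as its untreated period. It cannot serve as evidence of effect as well.

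**Step 3: size, under a stated condition.** The article gives no alpha, so there is no figure of its own to reproduce. Assume two-sided 0.05 per test, one score per instrument, and that any positive primary result is read as success. For k independent tests, the chance of at least one false positive is 1 − 0.95^k.

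- k = 3 (outcomes with an effect question, one test each): 1 − 0.95^3 = 14.3%
- k = 4 (constructs, one test each): 1 − 0.95^4 = 18.5%
- k = 5 (instruments, one test each): 1 − 0.95^5 = 22.6%
- k = 15 (five instruments, three contrasts each): 1 − 0.95^15 = 53.7%, an upper bound

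**Step 4: allowing for correlation.** A multivariate normal simulation (400,000 draws) used assumed correlations between outcomes and 0.5 between contrasts that share a baseline.

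| Tests | Outcome correlation 0 | 0.3 | 0.7 |
|---|---|---|---|
| 3 outcomes, 1 contrast | 14.3% | 13.6% | 10.9% |
| 5 instruments, 1 contrast | 22.7% | 20.8% | 14.9% |
| 3 outcomes, 3 contrasts | 33.0% | 31.7% | 25.9% |
| 5 instruments, 3 contrasts | 48.8% | 45.7% | 33.8% |

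Every scenario exceeds 5%.

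**Step 5: what error control costs.** With the planned stage 3 sample of 960, 80% power and a paired comparison, the detectable standardised change is (z for alpha + 0.842)/√960, where √960 = 30.98.

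- alpha 0.05: (1.960 + 0.842)/30.98 = 0.09
- alpha 0.01 (0.05/5): (2.576 + 0.842)/30.98 = 0.11

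If only 480 complete (an assumed loss of half), the same figures are 0.13 and 0.16.

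**The case against.** The best defence is that this is a condensed article. The alpha level, the adjustment method and the order of testing are commonly left to an analysis plan, which is not shown. That stands: the missing adjustment is not itself an error, and several primary outcomes are not wrong as such. The defence does not reach the conflict over digital health literacy, which lies between sections of this document, or the list of primaries, which the article fixes itself.

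A reader might go further than the text allows in four ways.

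- **That one chance result out of about 15 tests would be declared success.** The article has no such rule. Questions 1 to 3 can each be answered on its own outcome, and the question about success comes without a criterion. The figures above are therefore conditional.
- **That 15 tests are planned and the error rate is 53.7%.** An omnibus variance analysis gives one test per outcome, t0 against t1 is essentially a pre-intervention comparison, and results from the same people are correlated.
- **That no time contrast is singled out anywhere.** The waitlist component does name t1 to t3 for the intervention group. What lacks a leading contrast is the main pre–post analysis.
- **That the self-developed instrument has unknown measurement properties.** The article refers to a supplement on validity and reliability, which is not available here, so this cannot be checked.

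**Conclusion.** The point holds in two parts. First, the outcome list, the stage 3 questions and the quantitative analysis section contradict one another on digital health literacy, and they must be reconciled. This part needs no assumption. Second, the main pre–post analysis has unranked primary outcomes and no leading contrast, so the article does not fix which result supports a claim of effectiveness.

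The size of the second part depends on a reading that the article leaves open. If any positive primary result counted, the false-positive chance would be 14.3% for the three outcomes with an effect question and 22.6% for all five instruments, with one independent test each at an assumed 0.05. Correlation brings these to about 11% and 15% at an outcome correlation of 0.7. Adding time contrasts raises them. The matter should be settled before stage 3 data are analysed.

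**What to change.** 1. Move the G-eHEALS and the holistic DHL instrument from the primary outcomes to predictors or exploratory measures, in line with question 4.
2. Name the change from t1 to t3 as the leading contrast for the WAI, WHOQOL-BREF and DASS-21 stress. The article already plans this contrast for the intervention group.
3. Make comparisons at t2 secondary. Label t0 to t1 as the pre-intervention comparison, not as evidence of effect.
4. Control error over the three outcomes by Holm or in a fixed order. Testing the WAI first is one reasonable option, since the article says of the intervention: "Its main aim is to improve the participation of those affected in their working life". It is not the only defensible choice, because quality of life and stress each have an effect question of their own.

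The cost is wording in the outcome and analysis sections and an update of the registered outcomes. Data collection does not change. The power loss is small: even at alpha 0.01, stricter than the 0.05/3 = 0.0167 of Holm's first step for three outcomes, the detectable change at 960 participants rises only from about 0.09 to about 0.11.
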